### Outcome assessment

While the pre-questionnaire will only contain questions on self-management related constructs and socio-demographics, the post-questionnaire will also measure the perceived usability and usefulness of the application. Both questionnaires will be administered online and take about 20 to 30 minutes. Pre-post-comparisons will be facilitated by the random and thus anonymous assignment of a unique code for each participant that has to be entered when starting the survey. The questionnaire was created in English and then translated. Where available, already validated translations were used. For those scales that were only available in English, back and forward translations by native speakers of both languages were applied.

#### Patient information

Basic recordings about the patients comprise information such as socio-demographic descriptions, number of physician consultations during the intervention phase, or his/her experience with using similar technologies. Besides, the usage of EMPOWER will be recorded for each participant, including the patient’s number of logins to the system, the duration of use per visit, or the number of goals entered into the system. The records will show how often and intense the system was actually used by participants, and allow conclusions about the most useful features of the tool. Subjectively reported information from the patients will then be compared to objectively collected data.

#### Usability

Usability will be measured using the System Usability Scale by Brooke [26]. The scale was developed to assess the usability of interactive systems and is commonly used for this purpose. It consists of ten items that ask for a subjective assessment of the system, e.g. how easy it was to use it or how well integrated the various features of the system are. Both, reliability and validity of the scale have been proven [27]. Questions to assess the perceived usefulness of the EMPOWER system are based on the Technology Acceptance Model [28,29]. The model considers why technological systems are accepted or rejected by its users and how certain characteristics of the system determine this process. To measure the perceived usefulness of the EMPOWER system ten items from Davis’ [29] short screening scale on technology acceptance are used and were slightly adapted to the purposes of EMPOWER.

To assess whether the participating physicians perceive the EMPOWER system as useful in fostering patients’ self-management semi-structured interviews will be conducted. This will be done during the intervention phase via short telephone interviews to gather current feedback on the tool and more detailed through face-to-face interviews after the intervention.

#### Empowerment

Patients’ empowerment will be measured using Spreitzer’s Empowerment Scale [30] and The Problem Areas in Diabetes (PAID) [31]. Spreitzer’s Empowerment Scale consists of twelve statements related to the patient’s perceived importance, control, management, and autonomy concerning his/her diabetes. The PAID asks the patient whether he/she perceives twenty aspects, such as being limited concerning nutrition or not having treatment goals, as current problems.

#### Self-management activities

The impact of patient empowerment on self-management activities through the use of the EMPOWER system will be assessed by measuring the patients’ pre- and post-intervention health status, diabetes self-care, health literacy, doctor-patient communication, and empowerment. To assess an overall effect of the application on the health status as perceived by the patient, a self-reported, one item measure will be used. Patients will be asked to rate their health independently from their diabetes to avoid negatively biased answers due to the chronic condition. Diabetes self-care will also be measured subjectively, using the SDSCA as developed by Toobert and Glasgow [32] and revised by Toobert and colleagues [33]. The scale focuses on the patients’ self-care across various dimensions such as diet, exercise, blood sugar testing, foot care, and smoking. The questions refer to the last seven days of a participant’s routine diabetes self-care and therefore represent a comprehensive insight into the patient’s self-management that will be completed by the objective data stemming from the user tracking.

#### Health literacy

As an adequate level of heath literacy is paramount for being an effective self-manager [34] possible changes in health literacy due to the use of the EMPOWER system are assessed. Therefore, the Newest Vital Sign (NVS) [35], an objective test of functional health literacy in form of a nutrition label will be employed. Further, a subjective measure consisting of three items related to the perceived ability to understand written medical information, namely the Chew Items [36,37], will be used. In order to gain insight in the patients’ knowledge specifically about diabetes a range of knowledge items will be asked. Doctor-patient communication will be measured with scales from Kaplan [38] and Heisler [39]. While the first one assesses a physician’s decision making style concerning the patient’s involvement in treatment decisions, the latter one focuses on the provider communication. It thus considers the patient’s satisfaction with his/her doctor’s communication concerning disease and treatment.

### Data analysis

Data will be analyzed using the statistics software package SPSS, version 21, from IBM. To detect possible changes and their predictors’ descriptive statistics and regression analyses will be applied. In order to compare pre- and post-results as well as control and intervention group dependent and independent t-tests will be calculated.

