### Study design

The study is planned as a pre-post-design by administering questionnaires before and after the intervention. The aim is to recruit up to 70 participants at both study sites and then randomly assign them to either the intervention or control group.

After being recruited participants will be asked to give their informed consent. They will then be administered an online questionnaire containing various measures on self-management and socio-demographics to assess their baseline values before using the EMPOWER system. In order to create familiarity with the tool all participants will take part in an introductory training. There, patients will be taught how to download, use, and integrate the application into their daily life.

Participants are supposed to use the system regularly for a period of three months. They will be contacted via telephone on a weekly basis to gather feedback on usability, discuss potential problems concerning the tool and reduce the loss to follow-up. After the intervention has ended patients are again asked to fill in an online questionnaire containing the same measures as the pre-questionnaire plus questions on usability and usefulness of the tool.

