### Recruitment

It is planned to recruit overall 140 patients. The calculation of 140 participants (70 patients at each study site) is based on a previous study by Schulz and colleagues [25] in the field of web-based interventions. Eligible participants are between 18 and 65 years of age and suffer from diabetes type 1 or 2. Moreover, they need to have access to internet, own a computer or smart phone and be able to use the EMPOWER application.

In Germany, participants will be recruited via the practice network GOIN in Ingolstadt, Bavaria. The network comprises about 500 medical specialists and general practitioners who care for about 200.000 patients. The administrative staff from the practice network will be in charge of the recruitment of the patients and physicians for the main study. This will be done through personal contact with network members and advertising in practices and the network’s magazine.

Turkish participants will be recruited at the Hitit University Endocrinology Clinic of Turkey in Ankara. The Turkish Ministry of Health collaborates with two endocrinologists, two diabetes nurses, and one dietician at the University hospital who will recruit the participants among their patients, and also hired participants for the pretest.

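### The group comparison is set as an unadjusted t-test, and the plan does not say that it, rather than the pre-post test, carries the effect claim

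*Protocol article*

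**What the plan says.** All references are to the protocol article. The Data analysis section has two operative sentences. The first plans regression: "To detect possible changes and their predictors’ descriptive statistics and regression analyses will be applied". The second assigns the comparisons to t-tests: "In order to compare pre- and post-results as well as control and intervention group dependent and independent t-tests will be calculated". No covariates are named, no test is marked as decisive, and it is not stated whether the independent t-test uses three-month scores or changes from baseline.

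The Study design section introduces the trial in pre-post terms ("The study is planned as a pre-post-design by administering questionnaires before and after the intervention"), although participants are to be recruited and the sponsor will then "randomly assign them to either the intervention or control group". The first questionnaire serves "to assess their baseline values before using the EMPOWER system"; the second is described as "containing the same measures as the pre-questionnaire plus questions on usability and usefulness of the tool". Under Outcome assessment, each person's two questionnaires can be linked: "Pre-post-comparisons will be facilitated by the random and thus anonymous assignment of a unique code for each participant". Under Recruitment, "It is planned to recruit overall 140 patients", 70 at each of the two country sites.

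The sections on self-management activities and health literacy describe the platform's impact through measurements before and after the intervention, without mentioning the control group.

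**The concern.** There are two issues, of different kinds.

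**Attribution.** A dependent t-test within the intervention arm measures change over three months from every cause: the platform, answering the same questionnaire twice, weekly telephone contact, and regression to the mean. The control group exists to separate these. Because the plan lists both tests without ranking them and describes impact in pre-post terms, a significant within-arm change could be reported as an effect of the platform.

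**Precision.** A t-test has no place for covariates. The baseline value of each repeated measure is collected and linkable, and site is known. A post-score t-test uses neither. A change-score t-test uses the baseline, but less efficiently than regression adjustment. The Limitations section itself expects dropout and warns that change over three months may be hard to detect, so avoidable loss of precision matters here.

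**Working it through.** **What can be reproduced.** The only stated figure is the total: 70 + 70 = 140. No effect size, SD, alpha, power or dropout rate is given, so the sample size cannot be rebuilt.

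**Assumptions (not in the documents).** 1:1 allocation, hence n = 70 per arm (the article gives 70 per site, not per arm); no dropout; two-sided alpha 0.05; true effect d = 0.4 SD; equal variances; pre-post correlation r from 0.3 to 0.7.

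**Between-arm power.** The noncentrality is d / √(2v/n), referred to the noncentral t distribution. In units of the outcome variance, v is 1 for post scores, 2(1 − r) for change scores and 1 − r² for ANCOVA. For post scores: 0.4 / √(2/70) = 0.4 / 0.169 = 2.366, power 65.2%.

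| r | Post-score t-test | Change-score t-test | ANCOVA |
|---|---|---|---|
| 0.3 | 65.2% | 51.0% (v = 1.40) | 69.3% (v = 0.91) |
| 0.5 | 65.2% | 65.2% (v = 1.00) | 77.4% (v = 0.75) |
| 0.6 | 65.2% | 74.8% (v = 0.80) | 83.6% (v = 0.64) |
| 0.7 | 65.2% | 85.9% (v = 0.60) | 90.8% (v = 0.51) |

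ANCOVA has the smallest v in every row. Against change scores the variance ratio is (1 − r²) / [2(1 − r)] = (1 + r)/2, which is below 1 whenever r < 1.

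**Site.** With two equal sites whose means differ by D SD, ignoring site multiplies the variance by 1 + D²/4. At D = 0.5 that is 1.0625, so site accounts for 0.0625 / 1.0625 = 5.9% of the total variance. By the normal approximation, power for 0.4 SD falls from 65.8% to 64.8%, 63.1% or 59.4% at D = 0.3, 0.5 or 0.8. This compares models without the baseline score. Once that is in the model, part of any site difference is already absorbed and the extra gain may be smaller.

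**Within-arm test when the platform does nothing.** Suppose both arms improve by s SD. The standardised paired shift is s / √(2(1 − r)), and the noncentrality is that value × √70, with 69 degrees of freedom. At r = 0.6:

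- s = 0.2: 0.2 / 0.894 = 0.224; noncentrality 1.871; significant 45.4% of the time.
- s = 0.3: 0.3 / 0.894 = 0.335; noncentrality 2.806; significant 79.0% of the time.

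The range for s = 0.2 to 0.3 is 37.8% to 69.7% at r = 0.5, and 56.8% to 89.2% at r = 0.7. A simulation of 4,000 trials (r = 0.5, s = 0.2, no platform effect) gave 38.2% for the paired test and 5.1% for the independent t-test between arms. The common shift therefore misleads only the within-arm test.

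**The case against.** The strongest reply is that the plan does compare randomised arms, and that comparison is sound. This stands. A shift common to both arms cancels, and the independent t-test keeps its 5% error rate. A reader might infer that the whole planned analysis credits time trends to the platform; the documents do not support that. Nor does any section adopt a rule such as calling the platform effective when change is significant in the intervention arm but not in the control arm. The pre-post wording in the outcome sections describes what is measured, not a decision rule.

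Second, regression is planned in the same section, and a condensed article may leave covariates to a fuller document. That stands in part: it cannot be said that baseline and site will go unused everywhere. But the stated purpose of the regression is change and its predictors, the abstract names log files and login counts as independent variables, and the sentence that follows gives the comparison of arms to t-tests. The point concerns that stated method, not a missing covariate list.

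Third, if change scores are meant, the baseline is used and the gain shrinks: at r = 0.7 it is about 5 percentage points (85.9% to 90.8%), not the 26 points seen against post scores. This also stands, and both comparisons are shown above.

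**Conclusion.** The point holds as a loss of precision in a valid between-arm test, together with a risk of misattribution because the plan does not say which test carries the claim. It is not a finding of bias in the randomised comparison.

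For a true 0.4 SD effect at r = 0.5 to 0.7, ANCOVA adds about 12 to 26 percentage points of power over a post-score t-test and about 5 to 12 points over a change-score t-test. Adjusting for site adds little. These sizes depend on the correlation, which the article does not give, and on 70 per arm with no dropout; fewer completers would lower every figure. The 45% to 79% false-positive range at r = 0.6 depends on an assumed common improvement and matters only if a within-arm result is presented as evidence of effect. The between-arm comparison removes the influence of the weekly calls only if both arms receive them, and the article does not settle that.

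**What to change.** In the Data analysis section, replace the t-test sentence with a statement on these lines: for each continuous outcome measured at both time points, the test of effect is the intervention-minus-control difference at three months, estimated by a linear model (ANCOVA) of the three-month score on arm, baseline score and site, and reported with a 95% confidence interval. Pre-post means and dependent t-tests within each arm are descriptive, and no claim of effect is drawn from them. Keep the planned regression on usage and other predictors as a separate, exploratory analysis.

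The cost is wording only. No new data are needed, the questionnaires are already linked by code, and the SPSS package named in the article fits the model. The change should be made before outcome data are examined.

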## Discussion

The interplay between multiple sources, including EHRs, patients’ own registered information and treating physicians’ recommendations on one platform can have important implications for general practice. By actively integrating these features in one comprehensive platform the EMPOWER system may not only improve self-management activities in diabetes patients but will also facilitate physician’s work by having all important information readily available on one platform. In addition, the system may help improve the relationship between doctor and patient and foster a more systematic discussion with the patient on further disease management strategies and potential intervention points.

### Limitations

Limitations are prone to occur with regard to patient recruitment. The intervention will have to foresee potential dropouts due to the length of the intervention and potential research overload on the side of the patient.

In addition, physicians are asked to be actively involved in the program but time constraints and resource limitations are likely to impact their involvement. Nevertheless, with regard to patient retention rates physicians are of crucial importance in order to promote and sustain the intervention.

Lastly, given the fairly short amount of time of three months, behavioral changes may not be easily detectable, therefore regular use of the EMPOWER system has to be made sure in form of reminders and regular updates regarding changes of the system.

## Abbreviations

EHR: Electronic health records
ICT: Information and communication technologies
ODL: Observations of daily living
PHR: Personal health records
